#### 3.3.2. Estimating Injury Rates

In the HIPI study [5], participants consented to researchers analyzing their ACC injury records as a condition of being part of the study, and these were provided by ACC for the analysis. For the MHIPI study, ACC provided anonymized injury records matched to addresses we supplied to them and all household members were potentially part of the study. The ACC injury data included the age group and sex of the claimant as well as an address identifier that was matched to information on the treatment arm and details of the modification applied once address information had been removed. Therefore, we cannot estimate fall injury rates per person-time as we have no adequate denominators. Instead, we will estimate injury rates at the household level. Although the data were anonymized for the MHIPI study, meaning that the total number of people whose injuries were potentially being assessed from the anonymized address lists was unknown, the mean number of consenting participants per household from the HIPI study was 2.2 overall, 3.1 for Māori and 2.1 for non-Māori households.

The treatment effect will be estimated by the SAS [11] procedure GENMOD by fitting a Poisson model with a log link function to injury counts at the household level with an offset that is the log of the length of the time interval over which the injury count was obtained. As with the HIPI study, where prior falls were an important predictor of falls during the trial period, a covariate in the model would be a count of fall injuries in the 365 days prior to the start of the trial for the given household. As it is possible that different tradesmen carrying out the intervention may undertake the modifications in slightly different ways, with differing degrees of effectiveness, a stratum variable will also be included as a covariate that discriminates between participants in Taranaki and those in Wellington. For the main analysis drawing on additional data for Māori households from the HIPI study, the stratum variable will take a third level. As the unit of randomization, the household, is also the unit for which rates are estimated, there is no clustering to be accounted for in this analysis.

As with the HIPI study analysis, we will also analyze rates of specific injuries (specific to the intervention) for the treatment and control groups, expecting the safety effect to be stronger for these injuries than for fall injuries, as it was for the HIPI study.

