#### 3.3.3. Odds of Fall Injuries

In the case of the sensitivity analysis of the odds of a home fall, the treatment effect will be estimated by the ratio of the odds of home fall injuries vs. other home injuries for the treatment group compared to the controls. We will use SAS regression procedures to calculate crude and adjusted odds ratios accounting for clustering at the individual and household level, such as GENMOD [11] with a REPEATED statement, which fits a GEE model to adjust standard errors for the effects of clustering. As we are analyzing the odds of fall injuries, we would expected some factors leading to correlations of injury rates within households, such as propensity to seek medical treatment, to have less of an effect (as they affect both numerators and denominators equally), leading to a smaller intraclass correlation coefficient (ICC).

An odds ratio less than one will indicate a safety effect from the intervention. We will also analyze the odds of specific injuries vs. non-fall home injuries using the same model specification.

This trial is registered, number ACTRN12609000779279.

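### The primary Poisson model for household fall counts makes no allowance for overdispersion, and having one record per household does not remove the need for it, so its standard errors are likely too small

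*Protocol article*

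**What the plan says.** Section 3.3.2 (Estimating Injury Rates) estimates the treatment effect in SAS GENMOD "by fitting a Poisson model with a log link function to injury counts at the household level". The offset is log follow-up time, and the covariates are the household's fall count in the previous 365 days and the regional stratum. The pooled analysis with the earlier HIPI trial adds a third stratum level, and specific injuries are analysed as rates too. No scale parameter, negative binomial dispersion or robust variance is named. The section closes its account of the model by saying that the household, as the randomized unit, "is also the unit for which rates are estimated, there is no clustering to be accounted for in this analysis".

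Three other statements in the article bear on the variance:

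- Household size is not available: "the total number of people whose injuries were potentially being assessed from the anonymized address lists was unknown", and so "we cannot estimate fall injury rates per person-time as we have no adequate denominators" (section 3.3.2).
- Fall risk differs between households. The prior count is included because of the HIPI trial, "where prior falls were an important predictor of falls during the trial period" (section 3.3.2).
- Section 3.3.3 refers to "some factors leading to correlations of injury rates within households, such as propensity to seek medical treatment". It expects these factors to matter less for the odds of a fall, because they act on numerator and denominator alike. It still uses GEE standard errors for that sensitivity analysis.

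**The concern.** A Poisson standard error is correct only if, after the covariates, the variance of the household count equals its mean. Summing over occupants does not remove the correlation between them or the tendency of one person to fall repeatedly. It moves both from the covariance between records into the variance of a single record. The statement about clustering answers whether the rows are independent, and leaves open whether each row has the assumed variance.

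The two analyses are also treated unevenly. The odds analysis, which the article expects to be less affected by within-household correlation, gets a corrected variance. The rate analysis, where that cancellation does not operate, gets none.

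At stake are the p-value and confidence interval for the primary outcome, for specific injuries, and for the pooled analysis, which section 3.3.2 calls the main one. The third stratum level there shifts the mean and does nothing for the variance. The trial is meant to inform a national programme (section 1), so a result that is significant only because its standard error is understated would have consequences.

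**Working it through.** **The plan's own figure.** Section 3.2 gives about 125 households per arm for a 26% change in the percentage of households with a fall injury (α 0.05, 80% power). The baseline percentage is not stated. With the usual two-proportion formula (two-sided, no continuity correction) and a 26% relative reduction, n = 125 is reproduced at a baseline of about 67%. An absolute 26-point change needs no more than about 57 per arm. The calculation concerns a percentage, so it says nothing about the dispersion of counts. As a rough anchor only, if 67% of households had at least one fall and counts were Poisson, the mean count would be −ln(0.33) = 1.11. That is 0.44 to 0.55 per household-year over 2.5 to 2 years.

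**Step 1: how heterogeneity enters.** If a household's expected count is μ·f, where f has mean 1 and variance c, then Var(Y) = μ + cμ², and the dispersion before covariates is φ = 1 + cμ. The article gives a mean of 3.1 consenting participants per Māori household in HIPI, but no spread. Taking size as 1 + Poisson(2.1) (assumed), c = 2.1/3.1² = 0.22. At 0.2, 0.4 and 0.6 falls per household-year over 2.5 years (assumed), μ = 0.5, 1.0 and 1.5, so φ = 1.11, 1.22 and 1.33 from household size alone.

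**Step 2: effect of residual φ on the Poisson test.** Type I error = 2[1 − Φ(1.96/√φ)]; interval width relative to the correct width = 1/√φ.

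| Residual φ | Type I error | Width ratio |
|---|---|---|
| 1.0 | 5.0% | 1.00 |
| 1.1 | 6.2% | 0.95 |
| 1.2 | 7.4% | 0.91 |
| 1.5 | 11.0% | 0.82 |
| 2.0 | 16.6% | 0.71 |

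**Step 3: do the planned covariates remove it?** The planned model was simulated under no treatment effect with 252 households (strata of 152 and 100), 2 to 3 years of follow-up, the offset, stratum and prior-year count; 3,000 runs per cell (Monte Carlo standard error about 0.4 points at 5%). Further heterogeneity is gamma with variance c. Each cell shows the type I error of the plain Poisson test, with the mean residual Pearson φ in brackets.

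| Source of heterogeneity | 0.2 per year | 0.4 per year | 0.6 per year |
|---|---|---|---|
| None | 5.0% (1.00) | 5.0% (1.00) | 4.7% (1.00) |
| Household size only | 5.8% (1.10) | 8.3% (1.20) | 7.9% (1.29) |
| Gamma, c = 0.5 | 8.0% (1.22) | 10.5% (1.41) | 11.8% (1.57) |
| Gamma, c = 1 | 10.0% (1.40) | 14.1% (1.70) | 17.9% (1.93) |
| Gamma, c = 1, plus size | 11.3% (1.50) | 16.1% (1.83) | 20.5% (2.08) |

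The covariates help but do not suffice. With c = 1 and μ = 1, φ falls from 1 + 1×1 = 2.0 to 1.70. For household size alone at the same rate it falls only from 1.22 to 1.20, because one year's count is a noisy proxy for underlying risk.

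A second simulation (126 per arm, 0.2 to 0.3 falls per household-year, 2.5 years, size varying throughout) gave 5.6% to 6.6% with size alone, and 9.6% to 14.0% with gamma variance 0.5 to 1.0 added.

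**Step 4: does a corrected variance work?** Over all scenarios of the first simulation, rejection rates were 4.6% to 6.9% with Pearson-scaled standard errors and 4.9% to 6.4% with sandwich standard errors. The negative binomial model was not simulated.

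**The case against.** The strongest reply is that the clustering sentence is correct. With one record per randomized household there are no correlated rows, and clustering and overdispersion are different matters. This stands. A reader might infer that the sentence is false and should be deleted, but the documents do not support that. It is true as far as it goes, and is incomplete as a reason for leaving the variance alone.

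A second reply is that a journal article need not list every model option, and that GENMOD with a Poisson distribution can carry a scale parameter or an empirical variance. This has some force: nothing in the article forbids them. However, the article names the distribution, offset and covariates, gives a reason why nothing further needs accounting for, and names a variance correction for the sensitivity analysis only. Followed as written, the primary analysis uses model-based Poisson standard errors.

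Third, the plan adjusts for prior falls and stratum, which deserves credit. Step 3 shows that this reduces the excess without removing it.

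Fourth, errors in address matching are tempting as a further source. Section 3.2.2 keeps 13 households linked to several address IDs (8 + 4 + 1) and sets 35 of 252 unmatched households to zero. But it attributes multiple IDs mainly to different ways of writing suburbs and towns, and calls the 35 an upper limit, some of them genuine zeros. These could add variation, but the documents do not allow its size to be stated, and the conclusion does not depend on it.

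**Conclusion.** The concern holds as a likely understatement of the standard errors. The direction is well supported by the article's own statements: risk differs between households, the number at risk is unknown, and injury rates correlate within households. An exact 5% test needs residual φ = 1, which those statements make implausible.

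The size is not known. The assumptions are 0.2 to 0.6 falls per household-year, household size as 1 + Poisson(2.1), and gamma variance of 0.5 to 1 where further heterogeneity is added. Under these, the two-sided type I error is about 6% to 8% from household size alone and about 8% to 20% with further heterogeneity. At the lowest rate with size alone, the excess is under one percentage point.

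Two stronger readings go too far. A reader might infer that the error will certainly exceed 5% by a definite amount, but the article gives no fall rate, variance or dispersion from which to say so. A reader might also infer that the estimated rate ratio is biased. The point concerns only its standard error, confidence interval and p-value.

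**What to change.** Keep the log-link GENMOD model, the offset and the covariates. Before the outcome data are analysed, prespecify one variance that allows for overdispersion. Poisson with empirical sandwich standard errors (REPEATED SUBJECT=household) is one option, and section 3.3.3 already names that statement; a negative binomial model is another. Use the same choice for falls, specific injuries and the pooled analysis, and report the estimated dispersion. Reword the clustering sentence along these lines: *each household contributes one record, so records are independent; extra-Poisson variation in household counts is allowed for by the stated variance estimator.*

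The cost is about one line of code and one sentence. Intervals widen by √φ: 1.10, 1.22 and 1.41 times at φ = 1.2, 1.5 and 2.0. A rate comparison with 80% power when φ = 1 then has Φ(2.80/√φ − 1.96) = 72.5%, 62.8% and 50.8%. That shortfall is already in the data if overdispersion is present; the plain Poisson interval would only hide it. If φ is near 1, almost nothing is lost.

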#### 3.3.3. Odds of Fall Injuries

In the case of the sensitivity analysis of the odds of a home fall, the treatment effect will be estimated by the ratio of the odds of home fall injuries vs. other home injuries for the treatment group compared to the controls. We will use SAS regression procedures to calculate crude and adjusted odds ratios accounting for clustering at the individual and household level, such as GENMOD [11] with a REPEATED statement, which fits a GEE model to adjust standard errors for the effects of clustering. As we are analyzing the odds of fall injuries, we would expected some factors leading to correlations of injury rates within households, such as propensity to seek medical treatment, to have less of an effect (as they affect both numerators and denominators equally), leading to a smaller intraclass correlation coefficient (ICC).

An odds ratio less than one will indicate a safety effect from the intervention. We will also analyze the odds of specific injuries vs. non-fall home injuries using the same model specification.

This trial is registered, number ACTRN12609000779279.

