A sensitivity analysis will be conducted of the odds of falls and the odds of specific injuries compared to all other medically treated home injuries. This will enable models to be fitted that control for age group, which was found to be an important factor in the analytical models used in the analysis of the HIPI study [5]. Such an analysis will lose a proportion of information compared to the primary analysis of injury rates because households without any home injury claims over the assessment period do not contribute data. As the current intervention being tested was designed to prevent injuries arising from falls, it can be assumed that other types of injuries that occur in the home (burns, scalds, poisoning, cuts, stings, strains, collisions, etc.) would be relatively unaffected by the intervention. Using an odds ratio as an outcome measure has the additional benefit of controlling for propensity to seek—or to be differentially referred for—medical treatment following an injury, which is known to vary between different population groups, and to be lower for Māori than for others [7]. As randomization was carried out at the household level and stratified only at the regional level, there is always the potential for the intervention and control groups to differ at random, according to important characteristics associated with fall rates, such as age. Analysis of the odds of a particular injury type or mechanism compared to other injury types or mechanisms, is common in road safety for the assessment of vehicle-related safety characteristics, for example [9].

In order to detect a change of 26% in the percentage of households with medically-treated injuries arising from falls (α of 0.05, 80% power), we calculated that a sample size of about 125 households in each of the two arms of the study (treatment and control groups) would be required.

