#### 3.2.1. Defining Falls and Specific Injuries

In the context of self-reports of falls, Lamb et al. [6] recommended that a fall should be defined as ‘‘an unexpected event in which the participants come to rest on the ground, floor, or lower level’’ and participants in studies using self-reported falls were recommended to be asked “In the past month, have you had any fall including a slip or trip in which you lost your balance and landed on the floor or ground or lower level?’’ These guidelines were used to classify injuries from the ACC claims data.

Key information on fall injuries is provided by a free text field on the ACC claim form to describe what happened, generally a single sentence. Using these text descriptions in conjunction with other fields in the ACC claims data, coders will classify injuries as either falls or injuries specific to the package of modifications [10]. As well as referring to the text descriptions, coders consider the fields listing the activity immediately preceding the injury (e.g., running/walking), the “cause” (e.g., tripping or stumbling), any contact with objects/people/animals (e.g., ground/floor), any “external agency” (e.g., stairs/steps) and a general injury diagnosis (e.g., contusion). These fields help identify the specific injuries, which are those potentially preventable by the package of modifications applied, including virtually all injuries occurring on outside steps and most falls occurring in bathrooms.

Generally, the specific injuries are a subset of the fall injuries. Some injuries classed as specific occur from loss of balance not necessarily resulting in the subject being on the ground or floor. Such injuries occur when balance is lost and the subject collides with an object, causing injury, or some musculoskeletal injury occurs, such as muscle/tendon/ligament strain, as a consequence of loss of balance. The specific injuries generally exclude those arising from gardening, trips on furniture or children’s toys. Consistent with loss of balance, as an essential aspect of the Lamb et al. [6] falls definition, we exclude injuries occurring when the subject was jumping (such as trampoline injuries), undertaking sporting activities, or deliberate injuries (e.g., being pushed).

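### The comparator in the odds analyses is worded inconsistently and, read literally, includes some injuries the package is meant to prevent; the resulting bias toward 1 is probably small

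*Protocol article*

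**What the plan says.** All references are to the protocol article.

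- **Section 3.2, Outcomes**, introduces a sensitivity analysis of "the odds of falls and the odds of specific injuries compared to all other medically treated home injuries". It justifies the method by assuming that "other types of injuries that occur in the home (burns, scalds, poisoning, cuts, stings, strains, collisions, etc.) would be relatively unaffected by the intervention".
- **Section 3.2.1, Defining Falls and Specific Injuries**, describes the specific injuries as those "which are those potentially preventable by the package of modifications applied". It says they are in general a subset of falls, but adds an exception: "Some injuries classed as specific occur from loss of balance not necessarily resulting in the subject being on the ground or floor". In these cases "the subject collides with an object, causing injury, or some musculoskeletal injury occurs, such as muscle/tendon/ligament strain". The same section says that specific injuries usually leave out gardening injuries and trips on furniture or toys, so some falls are not specific.
- **Section 3.3.3, Odds of Fall Injuries**, estimates the treatment effect from "the odds of home fall injuries vs. other home injuries for the treatment group compared to the controls", and then adds: "We will also analyze the odds of specific injuries vs. non-fall home injuries using the same model specification".

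**The concern.** An odds ratio of target injuries against other injuries estimates the effect on the target only if treatment leaves the other injuries alone. The article says this itself in section 3.2. Yet strains and collisions appear in that section as unaffected, and in section 3.2.1 some of them appear as preventable.

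Three things follow from the literal wording:

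1. In the fall model, preventable non-fall injuries sit in the comparator.
2. In the specific-injury model, the same injuries meet the description of both case and comparator.
3. The comparator for specific injuries is worded in two ways, which differ over the non-specific falls.

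Section 3.2 gives the odds analysis two tasks: adjusting for age group, which the household rate model does not do, and controlling for propensity to seek treatment. If its comparator also shrinks under treatment, part of a real benefit is hidden, and two analysts following the text could report different odds ratios.

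**Working it through.** **Step 1: where each kind of injury falls.** The article gives no figure for these analyses that could be reproduced, so the first check is to apply the wording to each kind of home injury.

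| Kind of injury | Fall model (3.3.3) | Specific-injury model (3.3.3) | Specific-injury model (3.2) |
|---|---|---|---|
| Fall, specific | case | case | case |
| Fall, not specific | case | left out | comparator, on one reading |
| Not a fall, specific | comparator | case and comparator | case |
| Neither | comparator | comparator | comparator |

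The third row is the overlap. The second row is the difference between the two sections.

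**Step 2: bias in the fall odds ratio.** Inputs:

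- True fall rate ratio 0.74, from the 26% reduction in the earlier HIPI trial (section 1).
- Rate ratio for specific injuries, RRs. The article expects a stronger effect than for falls (section 3.3.2) but gives no size. Assumed 0.6, with a range of 0.5 to 0.74.
- Share s of control-arm comparator injuries that are specific but not falls. Not given. Assumed 1% to 20%.

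The treatment-to-control ratio of comparator injuries is 1 − s + s × RRs, so

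expected OR = 0.74 / (1 − s + s × RRs).

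With RRs = 0.6:

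- s = 1%: 0.74 / 0.996 = 0.743
- s = 5%: 0.74 / 0.98 = 0.755
- s = 10%: 0.74 / 0.96 = 0.771
- s = 20%: 0.74 / 0.92 = 0.804

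Over RRs from 0.74 down to 0.5, the result is 0.750 to 0.759 at s = 5% and 0.781 to 0.822 at s = 20%. With RRs = 1 the denominator is 1 and there is no bias.

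**Step 3: specific-injury odds ratio, non-fall comparator (section 3.3.3).** If the overlapping injuries are kept in the comparator, a true 0.60 becomes 0.60 / (1 − s + 0.6s). This is 0.602, 0.612, 0.625 and 0.652 at s = 1%, 5%, 10% and 20%. If each overlapping injury is coded as a case only, the result stays at 0.60.

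**Step 4: specific-injury odds ratio, all-other comparator (section 3.2).** Let g be the share of non-specific falls in the comparator and RRg their rate ratio. Then OR = 0.60 / (1 − g + g × RRg). If RRg = 1, the result is 0.60 for any g. With assumed RRg = 0.8 and g = 30%, it is 0.60 / 0.94 = 0.638.

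RRg should not be set to 0.74, because that is the effect on all falls together. If half of falls are specific (assumed) with rate ratio 0.60, then 0.5 × 0.60 + 0.5 × RRg = 0.74 gives RRg = 0.88. The odds ratio is then 0.60 / 0.976 = 0.615 at g = 20% and 0.60 / 0.952 = 0.630 at g = 40%.

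**The case against.** The best defence is that this is loose wording about a minor group of injuries in a supporting analysis. Its parts deserve separate answers.

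- **The overlap is an exception.** Section 3.2.1 says specific injuries are generally falls, and the comparator also holds burns, cuts, poisonings, stings and all the other strains and collisions. This stands, and it makes the low end of the range the more plausible.
- **Natural coding settles the double membership.** In a model of specific injuries an analyst would code a specific injury as a case. This also stands. A reader might infer that the specific-injury odds ratio is undefined; that goes too far, although the coding rule is left to be guessed.
- **Section 3.2 can be read as other than both falls and specific injuries.** It can, and that reading removes the problem. But section 3.3.3 does not adopt it, and its comparator for falls still takes in the non-fall specific injuries.
- **Strains and collisions can be broadly unaffected while a few are preventable.** This is true and softens the conflict between the two sections. It does not tell the analyst where to put those few.
- **Claim coding belongs in an analysis plan.** Fine detail does. Here, however, the article states a comparator, states it in two ways, and one of them conflicts with its own injury definition.

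**Conclusion.** The concern holds as an inconsistency with a conservative bias, probably small. Followed literally, section 3.3.3 biases the fall odds ratio toward 1 whenever the package prevents non-fall specific injuries. From a true 0.74 the shift is to 0.743 to 0.755 at an assumed 1% to 5% overlap, and to 0.804 at 20%, with an assumed specific-injury rate ratio of 0.6. The article gives neither the overlap share nor that rate ratio, so these figures show a range and are not estimates.

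A reader might infer that the odds analysis could contradict a true effect, or that the trial's main result is affected. The documents support neither. Every value above stays below 1, so the expected odds ratio keeps its direction. There is no bias if the package has no effect. The primary household Poisson model uses no comparator injuries, and its covariate for falls in the prior year may capture part of the propensity to claim.

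**What to change.** In sections 3.2 and 3.3.3, define one comparator for both odds analyses: home injuries that are neither falls nor specific injuries. Leave non-fall specific injuries out of the fall model, and non-specific falls out of the specific-injury model. The same sentence could say whether events excluded from the fall definition, such as syncopal, jumping or sporting injuries, count in the comparator.

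The coders already classify falls and specific injuries, so no new data are needed. The cost is slightly fewer injuries in the fall model and its comparator. The rule should be fixed before the outcome data are analysed, so that the comparator is not chosen with results in view.

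Optionally, fit the household rate model to the comparator injuries as a negative control, expecting a rate ratio near 1. That would test the assumption that these injuries are unaffected, at the cost of one extra model.
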